| *Follow up Phase*  The last clinical visit at the 12^th^ (T_5_) month may be a physical clinical visit or teleconsultation, depending on the doctor’s decision. Patient will be asked to complete a post-treatment quality of life online survey (approximately 10-15 minutes) during this visit. There will be a window period of ± 30 days for the last clinic visit. Please refer to Figure 1 for the study timeline. |  |
| **iii. Post Study Follow up and Procedures** |  |
| If there are any unresolved adverse events that require medical intervention, follow-up visits will be conducted and verified through the electronic medical records of their hospitalisation.  In the case of serious adverse events, this will be reported to the DSRB as soon as possible, no later than 7 calendar days after first knowledge by the investigator, and any additional relevant information about the event should be reported within 8 calendar days of making the initial report.  Patients’ clinical information and personal data may be combined or linked with, including but not limited to: government administrative data and research data such as, nation-wide health-related databases, economic data and National Autoimmune Registry, up to 31 December 2043. The linkage may be carried out by itself or with the assistance of a data intermediary. The collection of such data is for the purposes of the current research study and will be collected prospectively. |  |
| **iv. Discontinuation Visit and Procedures** |  |
| A discontinuation visit will be conducted for all patients who discontinued the study drug or withdrawn from the study regardless of whether it is voluntary based on patient’s request or decided by the Investigators for safety or non-compliance issues to follow-up on:   - Balance medication and packaging retrieval to do medication accounting and checking for adherence to assigned treatment arm - Existing AE(s) /SAE or complaints that are not resolved and to ensure that care assessment with support care delivery is continued until the problem is resolved. - Reason for withdrawal (if requested by the patient) |  |
| **TRIAL MATERIALS** |  |
| Trial Product (s) The investigational product (IP) and Auxiliary Product (AP) will be procured locally from NUH pharmacy and stored at NUHS Investigational Medicine (IMU) facility. |  |

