| **UPIRTSO events** refers to problems, in general, to include any incident, experience, or outcome (including adverse events) that meets ALL of the following criteria:   1. **Unexpected** 2. Pregnancy   In the event that the patient becomes pregnant during the study period, although very unlikely (patient will be screened for pregnancy before treatment phase and checked for pregnancy status at each clinical visit), patient will be withdrawn from the trial immediately. However, patient will be advised by their doctor or study investigator(s) on the procedures to stop medication.   1. Cancer   In the event that the patient is diagnosed with cancer during the study period, patient will be withdrawn from the trial immediately. However, patient will be advised by their doctor or study investigator(s) on the procedures to stop medication.   1. Fall risks   In the event that the patient falls during the treatment phase due to the side effect, doctor or study investigator(s) will assess and evaluate the severity of the fall before advising on the continuation of the study drug.  Expedited reporting to the IRB will be done as soon as possible, and not later than 7 calendar days after first knowledge by study investigator(s).   1. **Related or possibly related to participation in the research**   Prednisolone may cause mood changes (confusion, depression), weight gain, fluid retention, nausea, vomiting, indigestion, easy bruising, blood or black, tarry tools, blurred vision, increased urination or thirst, muscle weakness or cramps and severe stomach pain.  Methotrexate may cause mouth ulcers, nausea, vomiting, abdominal pain, diarrhoea, rash, hair loss, easy bruising, severe sore throat, tiredness, paleness, yellow eyes, tea-coloured urine, constant abdominal pain, risk of infection and breathlessness or persistent dry cough.   1. **Risk of harm**   Both prednisolone and methotrexate have been widely used clinically for treatments of other diseases and have a good safety profile.  The study investigators will make every effort to mitigate risks and ensure that the inclusion and exclusion criteria are strictly adhered to. Study investigators will also conduct close monitoring on the patients’ well-being during the clinical visits.  **Reporting Timeline for UPIRTSO Events to the NHG DSRB.**   1. Urgent Reporting: All SAE(s) listed whether related to or not to the study will be reported to IRB within 24 hours after first knowledge by study investigator(s):  - Results in death. - Is life-threatening (immediate risk of death). - Requires inpatient hospitalization or prolongation of existing hospitalization. - Results in persistent or significant disability/incapacity. - Is a medically important event.  1. Expedited Reporting: All collected study AE(s) will be reported as soon as possible, but not later than 7 calendar days after first knowledge by the study investigator(s). |  |

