| Collecting, Recording and Reporting of Serious Adverse Events (SAEs) to the Health Science Authority (HSA) |  |
| A serious adverse event or serious adverse drug reaction is any untoward medical occurrence at any dose that:   - Results in death. - Is life-threatening (immediate risk of death). - Requires inpatient hospitalization or prolongation of existing hospitalization. - Results in persistent or significant disability/incapacity. - Results in congenital anomaly/birth defect - Is a medically important event.   All SAEs that are unexpected and related to the study drug will be reported. The investigator is responsible for informing HSA no later than 15 calendar days after first knowledge that the case qualifies for expedited reporting. Follow-information will be actively sought and submitted as it becomes available. For fatal or life-threatening cases, HSA will be notified as soon as possible but no later than 7 calendar days after first knowledge that a case qualifies, followed by a complete report within 8 additional calendar days. |  |
| Safety Monitoring Plan |  |

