| Patients who consented to the study would have to undergo a few laboratory tests and procedures at the baseline visit to ensure that they meet the inclusion and exclusion criteria. One of the safety precaution tests conducted would be a pregnancy test to ensure that patient is not pregnant before consumption of drugs from either arm. The drugs used in this trial may impair fetal development, if patient is pregnant.  Methotrexate may occasionally lower blood count and cause liver inflammation. To detect these symptoms early, patients under the methotrexate arm is required to undergo a blood test on the 1^st^ (T_1_), 2^nd^ (T_2_), 3^rd^ (T_3_) and 6^th^ (T_4_) month. If an increase in dosage in methotrexate is required by the doctor, patients will continue to undergo a blood test as per doctor’s request.  An independent data monitoring committee which composes of biostatistician and clinical experts will be established to monitor the study progress, compliance, and data governance. The committee will meet on regular basis and will be responsible for independently evaluation of the safety for the patients participating in the clinical trial. Recommendation and concerns will be made by the committee for the study conduct and enrolment. In addition, the committee will regularly review the study Adverse Events (AEs) and Serious Adverse Events (SAEs). Investigator will be responsible to report relevant AE and SAE to the ethic board (DSRB and HSA) in accordance with the reporting requirement. |  |
| Complaint Handling |  |
| On the Informed Consent Form, there will be a contact number given that patient can raise their concerns to. A team will be designated to address the compliant, if any. All complaints will be kept anonymous. |  |
|  |  |
| **DATA ANALYSIS** |  |
| Data Quality Assurance |  |
| NUHS REDCap will be used to capture recruitment and relevant clinical data. The data will be routinely checked by study coordinators and study team members for accuracy and completeness of data. This IT system complies with applicable institutional data security, privacy, confidentiality, integrity and quality at NUHS cluster. FormSG will be used for the pre-treatment and post-treatment online surveys to capture patient related outcome measures. |  |
| Data Entry and Storage |  |

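### Section 9.2 withdraws a patient who becomes pregnant and no section provides for recording the pregnancy outcome, although fetal harm is a named risk and birth defect an SAE criterion

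*Protocol*

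**What the plan says.** - **Pregnancy (protocol section 9.2, first UPIRTSO criterion).** Pregnancy is listed as an unexpected event. The rule reads "checked for pregnancy status at each clinical visit), patient will be withdrawn from the trial immediately". The only further step given is that the "patient will be advised by their doctor or study investigator(s) on the procedures to stop medication".
- **Fetal risk (section 9.4).** "The drugs used in this trial may impair fetal development, if patient is pregnant". The sentence covers the drugs of both arms.
- **SAE criteria (section 9.3, reporting to HSA).** The list includes "Results in congenital anomaly/birth defect". What goes to HSA is limited: "All SAEs that are unexpected and related to the study drug will be reported". For such cases, "Follow-information will be actively sought and submitted as it becomes available".
- **SAE criteria (section 9.2, reporting to the ethics board).** "All SAE(s) listed whether related to or not to the study will be reported to IRB within 24 hours". The list that follows has five criteria, and birth defect is not among them.
- **Staying in the study after stopping drug (section 3.5).** Patients who stop for serious allergy, an adverse drug reaction or ventilator support are kept in the study for outcome data. Pregnancy is not on that list.
- **After the study (section 6.3 iii).** "If there are any unresolved adverse events that require medical intervention, follow-up visits will be conducted and verified through the electronic medical records". The same section allows patients' data to be linked with national databases up to 31 December 2043, and gives 7 calendar days for reporting SAEs to the DSRB.
- **Discontinuation visit (section 6.3 iv).** It is held for every patient who stops drug or withdraws, and covers medication accounting, existing unresolved AEs, SAEs or complaints, and the reason for withdrawal.

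**The concern.** The protocol names a harm and makes it an SAE criterion, yet it ends participation at a point when that harm usually cannot yet be seen. A birth defect becomes known at or near the end of pregnancy, and withdrawal takes effect when the pregnancy is detected. Section 3.5 already recognises that a patient can stop the drug and still supply data, but it does not apply this to pregnancy.

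What is at stake is the safety record. If a pregnancy occurs and nobody is asked to record its outcome, a report of no birth defects could reflect absence of follow-up rather than absence of harm. The mismatch between the SAE lists adds a second weakness. The ethics board's 24-hour route does not name the one event for which section 9.3 has a specific line.

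**Working it through.** **1. Does any stated route reach the birth outcome?**

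| Route | Scope as written | Reaches the birth outcome? |
|---|---|---|
| 3.5, retention for outcome data | Allergy, adverse drug reaction, ventilator support | No; pregnancy not listed |
| 6.3 iv, discontinuation visit | AEs, SAEs or complaints existing at that visit, followed until resolved | Not reliably; an uncomplicated pregnancy is not clearly an AE, and a birth defect is not yet known |
| 6.3 iii, post-study follow-up | Unresolved AEs that need medical intervention | Not reliably, for the same reason |
| 6.3 iii, data linkage | Optional; patients' data | Not reliably; infants' data and birth outcomes are not named |
| 9.3, follow-up information | Cases that qualify for HSA reporting | Only once someone has learned of the event |

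Timing points the same way. Taking about 9 months from conception to birth (an assumption), and follow-up to month 12 (Figure 1), 12 − 9 = 3. A conception after about month 3 would end after the last visit even if the patient had not been withdrawn.

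**2. Do the SAE lists agree?**

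| Criterion | 9.2 (24 hours, ethics board) | 9.3 (HSA) |
|---|---|---|
| Death | yes | yes |
| Life-threatening | yes | yes |
| Hospitalisation or its prolongation | yes | yes |
| Disability or incapacity | yes | yes |
| Birth defect | **no** | yes |
| Medically important | yes | yes |

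The lists differ by exactly one item. The time limit for reporting SAEs to the ethics board also differs: 24 hours in section 9.2, 7 calendar days in section 6.3 iii.

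**3. How often might this arise?**

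The protocol gives no pregnancy rate, so 1%, 3% and 5% per patient-year are assumptions. The number of patients is 40 (section 3.1). Planned treatment is about 3 months: six 2-week steps of prednisolone, or one plus two months of methotrexate. Section 6.3 allows continuation to month 6.

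- Patient-years on drug: 40 × 3/12 = 10; 40 × 6/12 = 20.
- Expected conceptions on drug = patient-years × rate.
- Chance of at least one = 1 − (1 − rate)^(patient-years).

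| Assumed rate | Expected, 3 months | Chance of ≥1, 3 months | Expected, 6 months | Chance of ≥1, 6 months |
|---|---|---|---|---|
| 1% | 0.1 | 1 − 0.99^10 ≈ 10% | 0.2 | 1 − 0.99^20 ≈ 18% |
| 3% | 0.3 | 1 − 0.97^10 ≈ 26% | 0.6 | 1 − 0.97^20 ≈ 46% |
| 5% | 0.5 | 1 − 0.95^10 ≈ 40% | 1.0 | 1 − 0.95^20 ≈ 64% |

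**The case against.** The strongest reply is that the protocol is silent on the pregnancy outcome and does not forbid its collection. A reader might infer that the outcome would never be collected, or that every pregnancy in the trial loses its outcome. The text does not support that. Every withdrawn patient has a discontinuation visit, unresolved events are followed, linkage is possible for many years, and follow-up information is sought on qualifying cases. This stands, and the claim is limited accordingly: the protocol states no procedure, and the general routes are not dependable.

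A reader might also infer that a known birth defect would fail to reach the ethics board within 24 hours. That too goes further than the text. The event could be judged medically important, or a significant disability, and both are on the section 9.2 list. Failing that, section 9.2 sends all collected AEs to the board within 7 days, and section 6.3 iii gives 7 days for SAEs. What remains is that 24-hour reporting of this event depends on judgement under another criterion. Reporting to HSA is likewise conditional on the event being unexpected and related.

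On size, counting all 40 patients for a full year gives 33%, 70% and 87% at the same assumed rates (1 − 0.99^40, 1 − 0.97^40, 1 − 0.95^40). Those figures are too high for conceptions on drug, because planned treatment lasts 3 months, possibly 6. Even the lower figures may be generous. Patients must test negative at baseline and are told not to become pregnant, and enrolment runs to age 60 and includes post-menopausal women. In the other direction, a relapse restarts treatment for 6 months, which lengthens exposure for some.

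Finally, section 11.2 plans no comparison of birth outcomes, and so few pregnancies could not support one. That is correct, and no efficacy conclusion depends on this point.

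**Conclusion.** The point holds as a gap and an inconsistency in the safety plan. Section 9.2 ends participation on pregnancy, no section provides for recording the outcome, and this works against the protocol's own statements in sections 9.3 and 9.4. The SAE lists differ by one item, birth defect, and the time limits for the ethics board differ (24 hours against 7 days).

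The expected number of conceptions on drug is 0.1 to 0.5 over 3 months and 0.2 to 1.0 over 6 months. This rests on assumed rates of 1% to 5% per patient-year, all 40 patients being at risk, and a constant rate over treatment. The reading of the follow-up routes needs no assumption about rates. The matter should be corrected because a single exposed pregnancy would be an important safety observation and the correction is cheap. It does not affect the comparison of the arms.

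**What to change.** Reconcile protocol sections 3.5, 6.3 iii and iv, 9.2 and 9.3 as follows.

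1. In section 9.2, separate the decision on study drug, left as written, from data collection. With the patient's consent, keep her in safety follow-up until the pregnancy outcome is known, and make section 3.5 agree.
2. Obtain the outcome by medical-record check, extending the use of records already described in section 6.3 iii. The linkage there names only patients' data, so the consent form needs wording that covers the birth outcome.
3. List any pregnancy outcomes individually, by allocated arm and drug received, without a between-arm test.
4. Make the SAE lists in sections 9.2 and 9.3 identical, and state one time limit for reporting SAEs to the ethics board in sections 9.2 and 6.3 iii.

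The cost is protocol and consent wording, plus one record check per pregnancy, probably none to two in all. No additional trial visits are needed.

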**STUDY PROTOCOL**

| **BACKGROUND AND RATIONALE** |  |
| --- | --- |
| Idiopathic granulomatous mastitis (IGM) is an inflammatory breast disease affecting mainly young to middle aged women in Asia^1^. The disease has a chronic recurrent course with multiple flares which inevitably affects the quality of life in these women who are usually in their reproductive years^2^. It is also a disfiguring illness with potential negative psychosocial impact on young women^3^. Its aetiology is poorly understood, and its treatment remains an enigma to breast physicians.  There is a myriad of therapeutic options for IGM such as antibiotics, steroids, non-steroidal anti-inflammatory drugs, immunosuppressants, aspiration or surgery^4^. However, there is currently no consensus on the ideal treatment to date. The lack of benefit from non-targeted antibiotic treatment has generally been accepted^3^. Surgery is commonly last resort due to the breast deformity from breast tissue volume loss, surgical scarring and despite these, the risk of recurrence persists postperatively^5^. Prednisolone is a common first-choice therapy however it is associated with multiple side-effects, frequent recurrences on discontinuation of therapy and may be associated with impaired quality of life^6^. Therefore, there is need to consider alternative treatment options with fewer adverse reactions and impact on quality of life.  Methotrexate is presently considered second-line therapy and appears to have fewer side-effects^7^. To date, there are a few reports describing the use of methotrexate at different stages in the disease. For example, switching of steroid therapy to methotrexate after a lack of response to corticosteroid treatment or following a relapse of disease on steroid therapy or used as combination with steroids^8^ during the initial treatment. However, methotrexate monotherapy or in combination with low doses of corticosteroids were rarely reported. Nonetheless, methotrexate use was found to be associated with a high complete response rate of up to 75%^9^ and relapse rates are significantly lower than prednisolone and surgeries^10^. |  |
| General Introduction |  |

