| The risk anticipated for the patients are:  1. All research techniques and medications have potential dangers and adverse effects. Blood collection may result in discomfort, bleeding, bruising, or swelling where the needle was inserted. Fainting may occur, and infections happen infrequently.  2. Allergic reactions can occur with any drug such as rash, itching etc.  3. Rarely, a severe and possibly life-threatening allergic reaction can occur. Symptoms of a severe reaction include: swelling of the face, difficulty breathing, or a sudden drop in blood pressure that may cause dizziness.  4. For the study drugs, there are some side effects that are unique to the drugs (prednisolone and methotrexate).  i) Prednisolone may cause mood changes (confusion, depression), weight gain, fluid retention, nausea, vomiting, indigestion, easy bruising, blood or black, tarry tools, blurred vision, increased urination or thirst, muscle weakness or cramps and severe stomach pain.  ii) Methotrexate may cause mouth ulcers, nausea, vomiting, abdominal pain, diarrhoea, rash, hair loss, easy bruising, severe sore throat, tiredness, paleness, yellow eyes, tea-coloured urine, constant abdominal pain, risk of infection and breathlessness or persistent dry cough. |  |
| **STUDY POPULATION** |  |
| List the number of subjects to be enrolled |  |
| 40 IGM patients, aged between 21 to 60 years will be recruited from NUH. |  |
| Criteria for Recruitment |  |
| Patients must have undergone biopsy and diagnosed with IGM. Eligible patients will be informed by their attending healthcare professional on the study during the clinic session. If patient is interest to join the study, a qualified study team member will then explain the study and obtain informed consent from the patient. Before beginning any study-related procedures, informed consent will be obtained. Patient will then be assigned a participant study code and randomised to a treatment arm. Recruitment will be done face-to-face in NUH at Breast Care Centre. |  |
| Inclusion Criteria |  |
| Patients will have to meet all of the following criteria below:   - Women, aged between 21 and 60 years - Positive diagnosis of idiopathic granulomatous mastitis based on histopathology results - Willing and able to give informed consent |  |
| Exclusion Criteria |  |

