| Patients who meet any of the following prerequisites will not be allowed to take part in this study:   - Women who are currently pregnant or breastfeeding - Cognitive impairment which prevents the patient from giving voluntary consent - History of any psychiatric conditions such as depression, psychosis, schizophrenia etc. - History of cancer in the past 5 years - History of abnormal renal or liver function - History of diabetes mellitus - Hepatitis B and/or Hepatitis C carrier - Diagnosed with tuberculosis (Positive microbiological evaluation for Grocott Methenamine Silver stain and Ziehl– Neelsen stain) - Any immunosuppressants or anti-inflammatory medications such as NSAIDS for the past 3 months - Concomitant medication that may have contraindication with prednisolone and methotrexate use |  |
| Withdrawal Criteria |  |
| Patients will be withdrawn from the study upon their request. However, data that has been collected until the time of withdrawal will be kept and analysed.  In cases of persistent non-compliance to dosing or study procedures, the data on non-compliance will be recorded, and the outcomes will be analysed based on intention-to-treat.  Under the following circumstances, patients will continue to be retained in the study to collect outcome data, but will be discontinued from taking the study drug:   - Serious allergic reaction to study drug requiring medical intervention and/or hospitalisation and as decided by investigators for safety reasons - Development of adverse drug reactions to the prescribed trial drugs which require medical intervention and as decided by investigators for safety reasons - Needing ventilator support upon hospitalisation, which prevents the consumption of tablets orally |  |
| Subject Replacement |  |
| There will be no replacement for patients who withdraw during the treatment period. |  |
|  |  |
| **4. TRIAL SCHEDULE** |  |

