| During the course of the study, patients on both treatment arms will be instructed to/advised:   1. Not get pregnant or try to get pregnant 2. No breastfeeding 3. Avoid alcohol 4. Inform the PI/Site PI/doctor before getting any vaccinations during study period 5. Strictly refrain from concurrent dosing with other medicines, including prescriptions, and to inform the investigator(s) immediately about any new medication they need/want to take 6. Take medication as per packaging instructions   For patients on methotrexate, an additional instruction of not consuming tolbutamide and/or co-trimoxazole will be given, due to possible drug interactions. |  |
| Blinding |  |
| This is a prospective pilot open label randomised trial. Patients and study team will not be blinded with regards to the treatment assigned. |  |
| Concomitant therapy |  |
| 20mg/day of omeprazole tablet will be taken with prednisolone tablet to reduce the irritation to the stomach caused by prednisolone.  5mg of folic acid tablet will be taken with methotrexate tablet every week to reduce bone marrow suppression. |  |
| **SAFETY MEASUREMENTS** |  |
| Definitions |  |
| Prednisolone and methotrexate have been widely used in local clinics for various diseases.    Prednisolone can be used to help reduce inflammation and reduce symptoms of swelling, redness and itchiness. It has been widely used to treat various diseases such as asthma, allergic conditions, skin problems, etc. It is also the standard of care treatment given to IGM patients in NUH and has a good safety profile.  Methotrexate is commonly used by rheumatologists for treatment of autoimmune diseases such as rheumatoid arthritis, systemic lupus erythematosus (SLE), etc.  Adverse events will be reported according to Common Terminology Criteria for Adverse Events (CTCAE) Version 5.0. |  |
| Collecting, Recording and Reporting of “Unanticipated Problems Involving Risk to Subjects or Others” – UPIRTSO events to the NHG Domain Specific Review Boards (DSRB) |  |

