| De-identified blood samples will be analysed and stored in NUH Tissue Repository. Recruitment and follow-up survey data will be collected electronically via NUHS REDCap. Only study team members with delegated rights will be able to access the data under the supervision of PI and Site-PI. All survey data will be collected electronically via FormSG. A copy of de-identified data will be stored in a secured server at NUH. |  |
|  |  |
| **SAMPLE SIZE AND STATISTICAL METHODS** |  |
| Determination of Sample Size |  |
| The prevalence rate of IGM in NUH is currently at 10 to 15 patients per year. Based on a stepped rule of thumb, a minimum sample size of 30 will provide at least 80% power to detect a medium standardised effect size of between 0.3 to 0.7 based on a randomised two-group comparison (Machin et al, 2021). Assuming a 20% attrition rate, the sample size required for this study is 36 patients. This will be rounded up to a sample size of 40 patients over a period of 36 months. |  |
| Statistical and Analytical Plans The primary outcome of 6-month clinical or radiological complete response will be compared between arms using Chi-square test. The effect estimate will be quantified in terms of difference in proportion as well as relative risk (RR) and their associated 95% confidence interval (CI). The secondary outcomes of time-to clinical or radiological response and time-to-relapse will be evaluated via the Kaplan-Meier method. The differences in survival curves will be compared using log rank test, with the effect estimate quantified in terms of hazard ratio and its 95% CI. The primary analysis of this trial will be based on Intention-to- Treat (ITT). A Per Protocol (PP) analysis will be performed on all patients who have completed 6 months of treatment regimen as a sensitivity analysis.  Chi square test will be used to evaluate the proportion of side effects and requirement for percutaneous or surgical intervention during treatment between arms. Modified Poisson regression will be used to identify clinical or biomarkers that are associated with treatment response and quantify the effect in terms of RR.  Patient reported outcomes will be reported via a survey on FormSG, conducted online. The questions will be adapted from SF36 V1 Singapore version and EORTC-BR23. Below are the domains to be compared:   - - General Health   - Physical Health   - Mental Health   - Body Image   - Sexual Image   - Breast Health |  |
| **ETHICAL CONSIDERATIONS** |  |

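### Section 11.1 plans 40 randomised patients in 36 months from a centre whose stated caseload gives 30 to 45 IGM patients in that time, with no allowance for ineligibility or refusal

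*Protocol*

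**What the plan says.** Section 11.1 (Determination of Sample Size) opens with the caseload: "The prevalence rate of IGM in NUH is currently at 10 to 15 patients per year". It takes 30 as the minimum size, then adds attrition: "Assuming a 20% attrition rate, the sample size required for this study is 36 patients". It ends: "This will be rounded up to a sample size of 40 patients over a period of 36 months".

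Section 3.1 names one source of patients: "40 IGM patients, aged between 21 to 60 years will be recruited from NUH". Section 5.1 puts 20 patients in each arm, and section 6.3 randomises only after screening is passed. The 40 are therefore randomised patients, and screen failures do not count towards them.

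Sections 3.3 and 3.4 require a histological diagnosis, age 21 to 60 and consent, and list ten exclusions. These include pregnancy or breastfeeding, any psychiatric history, diabetes, abnormal renal or liver function, and hepatitis B or C carriage. A further one reads: "Any immunosuppressants or anti-inflammatory medications such as NSAIDS for the past 3 months". Section 3.6 provides no replacement for patients who withdraw during treatment.

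**The concern.** The caseload and the target stand in the same short paragraph and are never compared. The caseload is described as IGM patients at the hospital, with no mention of eligibility or consent. The target counts patients who have passed every criterion, consented and been randomised. The step between the two, an eligible and consenting fraction, is absent.

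If the target is not reached in the stated period, either the period grows or the trial is analysed with fewer patients. In the second case the difference in 6-month response, the primary comparison in section 11.2, is estimated less precisely than a reader of the protocol would expect. Under-recruitment of this kind costs precision and does not by itself bias the comparison. It does mean that those approving the trial are shown a size that the stated caseload hardly supports.

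**Working it through.** **Inputs from the protocol.** Caseload 10 to 15 per year, base size 30, attrition 20%, target 40, period 36 months (all 11.1); one recruiting hospital (3.1). The midpoint of 12.5 per year is added here.

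**Assumption.** The share of cases that are eligible and consent is not given. Values of 100%, 80%, 70% and 50% are shown.

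**The plan's own size.** 30 × 1.2 = 36, the stated figure. Dividing by the retained share gives 30 / 0.8 = 37.5, so 38. The rounded 40 covers both, so this step does no harm.

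**Cases available in 36 months.** 3 × 10 = 30; 3 × 12.5 = 37.5; 3 × 15 = 45.

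**Share of all cases needed.**
- For 40: 40/30 = 133%; 40/37.5 = 107%; 40/45 = 89%.
- For 36: 36/30 = 120%; 36/37.5 = 96%; 36/45 = 80%.
- For 30: 30/30 = 100%; 30/37.5 = 80%; 30/45 = 67%.

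**Chance of reaching each number.** Enrolment is taken as Poisson with mean = caseload × 3 × share enrolled.

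| Share enrolled | Cases per year | Mean enrolled | P(≥30) | P(≥36) | P(≥40) | Months for 40 |
|---|---|---|---|---|---|---|
| 100% | 10 | 30 | 52% | 16% | 5% | 48 |
| 100% | 12.5 | 37.5 | 91% | 62% | 36% | 38 |
| 100% | 15 | 45 | 99% | 93% | 79% | 32 |
| 80% | 10 | 24 | 13% | 1% | 0.2% | 60 |
| 80% | 12.5 | 30 | 52% | 16% | 5% | 48 |
| 80% | 15 | 36 | 86% | 52% | 27% | 40 |
| 70% | 10 | 21 | 4% | 0.2% | 0.01% | 69 |
| 70% | 12.5 | 26.25 | 26% | 4% | 0.7% | 55 |
| 70% | 15 | 31.5 | 63% | 23% | 8% | 46 |

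Months for 40 = 12 × 40 / (cases per year × share enrolled). At 50% enrolled the means are 15, 18.75 and 22.5, and P(≥40) is below 0.1% at every rate.

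**Precision.** The 95% half-width for a difference in proportions with n per arm is 1.96 × √(2 × p(1 − p)/n). With an illustrative p = 0.75 in each arm, √(0.375/n) gives:
- n = 20: 1.96 × 0.137 = 27 points
- n = 15: 1.96 × 0.158 = 31 points
- n = 10: 1.96 × 0.194 = 38 points

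**The case against.** The strongest reply is that the target is optimistic but attainable. At 15 per year with every case enrolled, 40 is reached with probability 79%; with 80% enrolled the mean is 36. The trial calls itself a pilot, and falling from 20 to 15 per arm widens the illustrative interval by only about 4 points. All of this stands. It limits the size of the problem, but it relies on the top of the caseload range together with nearly complete uptake.

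A reader might infer more than the documents support:

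- **That even 30 is out of reach.** At 80% enrolled, the chance of reaching 30 runs from 13% to 86% across the stated caseload range, so this does not follow.
- **That the trial will close far short.** Section 11.1 gives a planned period and no rule that recruitment stops at its end. Section 9.4 has a monitoring committee that advises on enrolment. Slow accrual could lengthen the trial instead.
- **That pre-treated patients are in the 10 to 15 and are lost.** Section 1 lists IGM therapies as "antibiotics, steroids, non-steroidal anti-inflammatory drugs, immunosuppressants, aspiration or surgery", and section 9.1 says of prednisolone: "It is also the standard of care treatment given to IGM patients in NUH". Neither shows drug exposure before enrolment. Prednisolone is also the control treatment, so a newly diagnosed patient could be randomised before starting it. Prior antibiotics are recorded at baseline and are not an exclusion. The protocol does not say who makes up the 10 to 15 and has no figure for prior steroid or NSAID use, so the loss from this criterion has no known size.
- **That only 24 months are available for accrual.** The text does not say whether the 36 months includes the 12-month follow-up. That needs to be stated, but a 24-month calculation has no basis in the text.

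The word prevalence is also ambiguous. If patients with chronic disease are counted again in later years, distinct patients over three years number fewer than 30 to 45, which would make the shortfall larger.

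**Conclusion.** The point holds as a defect of planning in 11.1. On the protocol's own figures, 40 randomised patients are 89% to 133% of every IGM case expected in 36 months. At the midpoint and the low end, the target exceeds the expected number of cases even if none is ineligible and none refuses; this part rests on no assumed uptake. The probabilities assume Poisson arrivals, and those below 100% enrolment use uptake values that the protocol does not give. At an assumed 80%, the 36 that 11.1 calls required is reached with probability 1%, 16% or 52% at 10, 12.5 or 15 per year, and 40 with 0.2%, 5% or 27%. Reaching 40 is unlikely, not impossible. The consequence is a longer trial or a less precise estimate.

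**What to change.** In section 11.1:

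1. Replace the all-cases figure with the number of patients per year at the site who meet 3.3 and 3.4, counted from its recent records, multiplied by a stated consent rate.
2. Restate the number expected in 36 months, or the period needed to randomise 40.
3. Say whether the 36 months includes the 12-month follow-up.
4. Give the 95% confidence interval half-width for the response difference at the expected number, with the response rate assumed.

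This costs a count from existing records and one revised paragraph. The downside is a less favourable stated size or a longer period. It is best done before recruitment starts, while size, duration and number of sites can still be changed. The medication exclusion in 3.4 should be left as it is: the documents show no contradiction in it and contain no data on prior use from which to judge it.
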